### Secondary Outcome Measures for Patients With Primary AUD

1. Mean units of alcohol per drinking days for participants with AUD at 3, 6, 9 and 12 months, computed from self-reports.

2. Mean number of days to the first drink for participants with AUD, computed from self-reports.

3. Number of hazardous drinking days (drinking in excess of the safe limits) from baseline for participants with AUD at 3, 6, 9 and 12 months, computed from self-reports.

4. Mean changes in the scores on the OCDS from baseline for participants with AUD at 3, 6, 9 and 12 months.

5. Mean changes in the scores on the Alcohol Abstinence Self-Efficacy Scale from baseline for participants with AUD at 3, 6, 9 and 12 months

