## Methods

### Study Design and Setting

This will be a longitudinal, prospective, parallel-design, two arm, placebo-controlled single-rater-blinded randomized clinical trial with a recruitment period of 6 months and an observation period of 12 months for each participant with two strata based on primary diagnosis of Major Depressive Disorder or AUD. Patients with AUD will be recruited from those completing the Northern Addiction Residential Treatment program located in Grande Prairie while patients with Depression will be recruited from those assessed for wait listing onto the Cognitive Behavior Therapy (CBT) program run by the Adult Mental Health Team in Fort McMurray. The study has received ethical clearance from the Health Ethics Research Board of the University of Alberta and operational approval from the AHS. All participants will provide informed written consent prior to randomization. The study has been registered with clinicaltrials.gov (NCT02327858) and will be executed according to the timelines specified in the Gantt chart in Table 1.

**Table 1 table1:** Gantt chart for supportive text message project.

		Year 1				Year 2				Year 3			
		Start Date-End Date				Start Date-End Date				Start Date-End Date			
Milestones		Q1	Q2	Q3	Q4	Q1	Q2	Q3	Q4	Q1	Q2	Q3	Q4

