### Inclusion Criteria

Persons aged 18 years and over who are able to provide informed consent will be eligible if they have been assessed and waitlisted for the CBT program in Fort McMurray and fulfill the DSM-5 diagnostic criteria for Major Depressive Disorder or who have completed the residential addiction treatment program located at the Northern Addiction Treatment Centre, fulfill the DSM-5 diagnostic criteria for AUD and are in the stage of change and are committed and motivated to give up alcohol. Participants must be familiar with or willing to learn how to receive text messages and be available for long-term intervention. Mobile phone handsets and top-up call credit of up to 10 dollars monthly will be provided to those who satisfy the inclusion criteria but do not have mobile phones*.*

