### Randomization and Blinding

Randomization will be stratified by primary diagnoses (Depression or AUD) using permuted blocks to ensure balance (1:1) between treatment and control groups within each condition under study. The randomization codes will be transmitted by an independent statistician via text message directly to the researcher. This will commence immediately after the participant has signed the consent form. A dedicated, password-protected phone line with a secure online backup will be used to transmit these messages.

The research assistant who sends the text messages will not be involved in the outcome assessments except to contact those receiving the supportive text messages for feedback on the benefits of the text messages. Participants cannot be blinded and treatment allocation will be made explicit to them. Outcome assessors will be blinded to treatment group allocation. To ensure this, treatment allocation will be concealed from the outcome assessor by blocking access to the database, which contains the randomization code, and all participants in the study will be asked not to reveal their treatment allocation to their assessor. Outside the assessments, outcome assessors will not participate in discussions with the participants in study forums. To test the success of blinding we will ask the assessor to guess the allocation group for each participant at 3, 6, 9 and 12-month follow-ups. Moreover, these assessors will not be involved in data analysis. After data collection is complete all data will undergo a blind review for the purposes of finalizing the planned analysis. Every effort will be taken to avoid incomplete data and methods of dealing with unanticipated missing data will be determined during the blind review of the data.

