### Sample Size

Consistent with the idea that this is a pilot study, the research will use the data that can be elicited from participants who can be enrolled within the existing resources [21]. The study will therefore be limited to a sample size of 120, with about 60 patients randomized from each primary diagnostic grouping.

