### Follow-up Assessments

At 3, 6, 9 and 12 months, a blinded researcher (a research psychologist) will contact all patients over the phone and assist them in completing a range of assessment tools relating to the primary and secondary outcome measures. The research assistant who randomized the patients will contact patients in the intervention group by telephone at 6 months to get their views on the usefulness of the supportive text messages. All patients will be similarly contacted regarding their satisfaction with their treatment using a semi-structured questionnaire. At 12 months, data related to each patient’s utilization of health services and their associated costs will be compiled from AHS administrative records by the blinded research associate.

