### Statistical Methods

Since it is unlikely that this pilot study will be powered to detect sufficiently small clinically relevant differences, the primary purpose of the statistical analysis for this pilot study will be a thorough descriptive analysis of the data, with a view to understanding the amount and mechanism for any missing data. In particular one of the goals will be to determine the feasibility of long-term impact of supportive text message treatment and follow up in this population. An analysis of missing data may help to determine how to improve follow-up and retention of patients in the full study.

A secondary goal will be to examine the patterns of the longitudinal data, which will guide the planned analysis for a full study (e.g. using a Generalized Estimating Equation [GEE] approach or a generalized linear mixed models [GLMM] approach). In particular for each outcome measure we will look at the correlation between successive time points. Analyses will be done within each diagnostic group separately.

A final goal will be to produce summary statistics for the longitudinal data, which will provide estimates for future sample size calculations. A clinically meaningful difference has already been determined as in the stated hypotheses for the full study. From this pilot study we will be able to estimate the variability in the estimates that we would expect to see, which will help to guide the sample size estimation.

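### Days to first drink is right-censored at 12 months, yet the plan summarises it as a plain mean with no horizon or time origin

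*Protocol article*

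**What the plan says.** In the protocol article, Secondary Outcome Measures for Patients With Primary AUD, item 2 reads "Mean number of days to the first drink for participants with AUD, computed from self-reports". The other four items in that list name the 3, 6, 9 and 12-month assessments; item 2 names no time point, horizon or starting point.

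Study Design and Setting fixes "an observation period of 12 months for each participant". Under Follow-up Assessments, "At 3, 6, 9 and 12 months, a blinded researcher (a research psychologist) will contact all patients over the phone". Under Inclusion Criteria, AUD participants have completed residential treatment and "are in the stage of change and are committed and motivated to give up alcohol".

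The nearest text on incomplete data is in Randomization and Blinding: "methods of dealing with unanticipated missing data will be determined during the blind review of the data". Statistical Methods says that "the primary purpose of the statistical analysis for this pilot study will be a thorough descriptive analysis of the data", and names GEE and GLMM only as examples for the full study. No time-to-event summary appears anywhere.

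Primary Outcome Measure counts cumulative abstinence duration (CAD), the companion abstinence outcome, from discharge from the residential program.

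**The concern.** Time to first drink is right-censored by design. In a group leaving residential treatment and motivated to stop drinking, some participants should reach 12 months without a drink, and others will be lost while still abstinent. Neither has an observed value to enter into a mean.

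Whoever computes the mean must therefore choose a rule. Averaging over drinkers only compares subgroups defined by what happened after randomization and leaves out the participants who did best; if the messages work, more of those are in the intervention arm. Entering the last contact date for those lost while abstinent treats the loss as a drink on that day. At stake is whether the reported between-arm difference describes the treatment or the coding rule.

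**Working it through.** The article gives no relapse rate, dropout rate or numerical target for this outcome, so there is no stated figure to reproduce. The relapse and dropout rates below are assumptions, shown over a range.

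**Inputs**
- Follow-up: 12 months, taken as 365 days (Study Design and Setting).
- Size: "sample size of 120, with about 60 patients randomized from each primary diagnostic grouping" (Sample Size), allocated 1:1 within diagnosis (Randomization and Blinding), so about 60/2 = 30 AUD participants per arm.
- Assumed: exponential time to first drink, with proportion p drinking by day 365.
- Assumed: independent exponential dropout, with proportion d lost by day 365 if nobody drank.

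**Step 1: drinkers-only mean against the restricted mean, no dropout**

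λ = −ln(1−p)/365. Drinkers-only mean = 1/λ − 365(1−p)/p. Restricted mean to day 365 = p/λ. Participants without a value = 30(1−p).

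For p = 0.7: 1/λ = 365/1.2040 = 303.2; drinkers only 303.2 − 156.4 = 146.7; restricted mean 0.7 × 303.2 = 212.2. For p = 0.5: 1/λ = 365/0.6931 = 526.6; drinkers only 526.6 − 365 = 161.6; restricted mean 0.5 × 526.6 = 263.3.

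| Relapse, control/intervention | No value, of 30 per arm | Drinkers-only difference (days) | Restricted-mean difference (days) |
|---|---|---|---|
| 60%/40% | 12/18 | 12.0 | 46.8 |
| 70%/50% | 9/15 | 14.8 | 51.1 |
| 80%/60% | 6/12 | 19.5 | 57.6 |

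The drinkers-only mean shows 12.0/46.8 = 26%, 14.8/51.1 = 29% and 19.5/57.6 = 34% of the restricted-mean difference. With smaller assumed effects the pattern is the same: 5 of 23 days at 50%/40%, 10 of 37 at 65%/50%, 16 of 45 at 80%/65%.

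**Step 2: participants lost while abstinent coded at last contact, never-drinkers at day 365**

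μ = −ln(1−d)/365. Mean = [1 − (1−p)(1−d)]/(λ+μ). With d = 0 this equals p/λ, so entering day 365 for fully followed never-drinkers gives the restricted mean exactly.

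Example at 50%/40% relapse with dropout 15% (control) and 30% (intervention):
- Control: 0.575 × 365/(0.6931 + 0.1625) = 245 days.
- Intervention: 0.58 × 365/(0.5108 + 0.3567) = 244 days.
- Difference: −1 day, against a true 23.

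| Relapse, control/intervention | True restricted-mean difference | Dropout 20%/20% | Dropout 30%/15% | Dropout 15%/30% |
|---|---|---|---|---|
| 50%/40% | 23 | 20 | 40 | −1 |
| 65%/50% | 37 | 33 | 49 | 14 |
| 80%/65% | 45 | 39 | 52 | 25 |

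Simulation with 1,000,000 participants per arm gave the same dropout columns. With equal dropout, 20/23, 33/37 and 39/45, or 87% to 89%, of the difference remains. With unequal dropout the error goes either way.

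**Step 3: the unrestricted mean**

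The mean without a horizon is 1/λ, or 527 and 715 days at 50%/40%. Both lie beyond the 365 days of follow-up and cannot be estimated without extrapolation, so a horizon has to be stated.

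**The case against.** The item is a one-line label in a condensed article. Censoring rules and estimators usually sit in a full protocol or SAP, and the blind review is meant to finalise the analysis. A 12-month restricted mean is itself a mean number of days to the first drink, so the label can be read in a valid way.

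Much of this stands, and it rules out several stronger readings:
- A reader might infer that abstinent participants will be dropped or miscoded. The article says neither.
- A reader might infer that every way of filling in a value is wrong. Day 365 for a never-drinker followed throughout is correct for the restricted mean; only those lost while abstinent remain a problem.
- A reader might take the figure of about 30% as the loss to expect. It applies only to a drinkers-only mean under assumed relapse rates.
- A reader might infer that the full trial's planning values will be wrong. Statistical Methods ties its sample-size summaries to the longitudinal data and its meaningful difference to the stated hypotheses, which concern BDI and CAD.

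The objection does not remove the point. The article itself names the statistic and, alone in its list, gives this item no time frame. The deferral to blind review covers unanticipated missing data, whereas never-drinkers are foreseeable and their data are not missing. GEE and GLMM, offered as examples for the full study, do not supply a censoring rule.

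**Conclusion.** The point holds in a limited form. The plan fixes a plain mean, without horizon or origin, for an outcome that some participants will not have reached when observation ends. The consequence depends on an unstated choice. A drinkers-only mean shows about 26% to 34% of the restricted-mean difference under 20-point assumed effects. Last-contact coding keeps 87% to 89% with 20% dropout in both arms, but ranges from −1 to 40 days around a true 23 when dropout is 15% in one arm and 30% in the other. These sizes rest on exponential relapse, independent dropout and assumed rates.

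Importance is low to moderate: this is one of five AUD-specific secondary outcomes, with no formal test attached, in a pilot whose analysis is mainly descriptive.

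**What to change.** Redefine item 2 as time to first drink, counted from discharge from the residential program so that it matches CAD, and censored at the last completed assessment or 12 months, whichever comes first. Counting from randomization instead would give the two abstinence outcomes different clocks.

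Report Kaplan-Meier curves by arm and the 12-month restricted mean per arm, with the difference and its 95% CI. Give the numbers never drinking and the numbers lost while abstinent in each arm. Those counts matter because Kaplan-Meier assumes that people lost while abstinent go on to drink at the same rate as those still followed, and the counts show how much rests on that. A Cox model or log-rank test is optional in a descriptive pilot.

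The cost is wording in the outcome and analysis sections. The outcome already requires the day of first drink from self-report, and the assessment calls are already scheduled.

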### Secondary Outcome Measures for Patients With Either Primary AUD or Primary Depression

1. Improved EQ-5D-5L scores from baseline. Health related Quality of Life will be measured in all groups at baseline, 3, 6, 9 and 12 months using the EQ-5D-5L (Canadian version).

2. Quantitative and qualitative data will be gathered from all participants in the intervention group using the semi-structured questionnaire in Multimedia Appendix 1 to assess their perceptions about how helpful or unhelpful the supportive text messages were to the course of their recovery.

### Other Exploratory Outcome Measures

1. Frequency of health services utilization at 3, 6, 9 and 12 months will be computed from self-reports and compared to the AHS administrative data on the frequency of health services utilization. We will be able to determine the usefulness and accuracy of self-report health utilization data in comparison with administrative data. Self-report data has the benefit of being available immediately.

2. The cost of health services utilization for patients in the intervention and control groups using the AHS administrative data.

3. Number of days absent from work at 3, 6, 9 and 12 months will be computed from self-reports.

### Statistical Methods

Since it is unlikely that this pilot study will be powered to detect sufficiently small clinically relevant differences, the primary purpose of the statistical analysis for this pilot study will be a thorough descriptive analysis of the data, with a view to understanding the amount and mechanism for any missing data. In particular one of the goals will be to determine the feasibility of long-term impact of supportive text message treatment and follow up in this population. An analysis of missing data may help to determine how to improve follow-up and retention of patients in the full study.

A secondary goal will be to examine the patterns of the longitudinal data, which will guide the planned analysis for a full study (e.g. using a Generalized Estimating Equation [GEE] approach or a generalized linear mixed models [GLMM] approach). In particular for each outcome measure we will look at the correlation between successive time points. Analyses will be done within each diagnostic group separately.

A final goal will be to produce summary statistics for the longitudinal data, which will provide estimates for future sample size calculations. A clinically meaningful difference has already been determined as in the stated hypotheses for the full study. From this pilot study we will be able to estimate the variability in the estimates that we would expect to see, which will help to guide the sample size estimation.

## Results

We expect the results for the primary, secondary and exploratory outcome measures to be available within 18 months of project commencement. It is expected that the results will shed further light on the feasibility of using automated supportive text message interventions in long-term care for patients with Depression and AUD. The results of the pilot trial will also inform the implementation of a full-scale multicenter clinical trial.

## Discussion

### Implementation Strategy

#### Overview

This research proposes a novel intervention that addresses a critical gap in care for Depression and AUD patients and their health care providers. The research seeks to test the delivery of responsive, effective, cost-efficient care that transcends geographic boundaries and makes available important psychological supports that would otherwise be inaccessible or significantly burdensome for patients to use, given their physical location or position on a waitlist. There has been excellent front-line support for this initiative during trial development. As part of an integrated knowledge translation approach [22], discussions between our team and health care practitioners (health addictions therapists, counselors, and nurses), directors, clinical leads, primary care practitioners, and others involved with the treatment of this patient population have generated important insights into the logistics and potential impact of delivering care through text messaging. The implementation plan for the research will occur in the phases described below.

#### Pre-Implementation Phase

The involvement of patients in the creation of therapeutic text messages alongside health care providers is a critical precursor for the intervention. Patient-direct interventions can enhance both the uptake of innovations into clinical practice [23, 24] and ensure that care is aligned with patient needs and values [25]. Ethics clearance has been received from the University of Alberta Ethics Review Board and AHS has granted operational approval for the project to proceed. Assembly and training of human resources to manage and support the study will also commence in this phase. The knowledge-to-action framework, based on planned action theory will guide the development and implementation of the research [26]. Staff working in both study centers will be recruited as research associates and trained to use assessment tools by the principal investigator who is a practicing psychiatrist.

The study will use internet-based text messaging infrastructure; our industry partner and AHS tech will be engaged at this stage to pilot test both the system and handsets to ensure full functionality and to troubleshoot potential issues in advance of the study commencement. Text message providers will be involved in testing and troubleshooting for potential issues. Advertisement of the research project targeted to patients will start, and communication about study commencement as well as tailored dissemination of study information to health care providers (general adult psychiatrists and primary care networks), zone leadership and operations will occur. Weekly, open research team meetings will commence during this phase to facilitate exchange, and to rapidly advance the work and/or troubleshoot as the need arises. The design of CBT and addictions-focused text messages will commence immediately between patients and practitioners. The intent of the text messages is to supplement therapist-patient interaction; therefore there will be a high degree of collaboration between patients and practitioners during this activity. Once the trial infrastructure is in place, a study commencement date will be determined and the research will be executed according to the details outlined in this protocol.

#### Implementation Phase

Implementation will commence with recruitment of patients who will undergo study orientation, baseline assessment, and data collection. The intervention will be randomized and delivered according to the methods outlined earlier. Scheduled, open research team meetings will provide a forum for practitioners who are supporting study participants. Given that the intervention is patient-focused, key measures arising from its use will be monitored as the study data is collected and assessed by the Trial Management Committee. Ongoing, scheduled communication between the recruitment sites and research team administrators will commence during this phase to support recruitment, address any challenges arising, and to optimize implementation. Feedback will be actively solicited from health care providers, zone leaders and operations through weekly open research team meetings and supplemented by brokering activity undertaken by research team staff. As the trial moves past the mid-study mark (and should trial data suggest it effective and feasible), discussions will commence concerning the scaling up of the intervention through a full-scale, multi-site randomized trial [27, 28, 29].

### Behavior Change

The paradigm for behavior change using text messages as a patient-direct intervention is consistent with a CBT approach and addictions counseling principles. These approaches will be rigorously evaluated to detect potential impact during the course of the research. We intend to have a less direct impact on practitioner behavior with the adoption of texting as we anticipate texts will be a desirable part of the suite of treatment and counseling tools available to support their work. There is a high degree of interest in this modality within the practitioner community; as such, the bulk of our interaction time with practitioners and counselors will be used to encourage bi-directional linkage and exchange between these clinicians and the research team in support of study participants. Given the automaticity of the messages, we do not anticipate the need for interventions to specifically modify practitioner behavior per se; we anticipate that our main role with respect to the practitioners will be to ensure they are well-supported with the research, appropriately apprised of all aspects of the technology and message delivery, consistent with a robust, integrated knowledge translation approach.

